|  | 
Klinikum Brandenburg (Amendment from August 2021: Changed to Klinik Hennigsdorf due to chance of cooperating physician), Lung Tumor Outpatient Clinic CVK and the Municipal Hospital Brandenburg). In addition, information material will be displayed on the wards that treat stroke and lung cancer patients. This will give interested persons the opportunity to actively contact for the study participation themselves.
 
Participation of informed patients:
The patient is directly approached for participation in the study. Upon inclusion, he/she declares his/her consent to the collection of the basic medical data, the questionnaire surveys, the collection of his/her health insurance data and, if necessary, qualitative data.
 
As a further option, the patient's family member can be included in the study as an additional study participant. Here, the patient declares his/her consent to the collection of his/her basic medical data and health insurance data as well as the consent that the caregiver can use the navigation in his/her interest. The caregiver declares his/her consent to answer the questionnaire surveys and, if necessary, qualitative data. Patient and caregiver can use the navigation.
 
Participation of patients who are not capable of giving informed consent:
If the patient himself/herself is incapable of giving informed consent and is legally represented by his/her caregiver, it is possible for the caregiver to participate in the study. In this case, the caregiver gives consent for the patient to have his/her basic medical data and health insurance data collected. For himself/herself, the caregiver declares his/her permission to answer the questionnaire surveys and, if necessary, qualitative data.
 
Participants will be randomized to the intervention arm or the control arm after giving informed consent.
 |

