|  | 
Randomization
 
Randomization will be performed within each patient group (stroke / lung cancer) stratified by center (Berlin, Brandenburg) and after inclusion of patient or family member as block randomization with changing block length in a ratio of 1:1. After inclusion of the patient by the study nurse, randomization will be performed by the Institute of Biometry and Clinical Epidemiology of the Charité. The randomization list is compiled by the biometricians involved. After randomization, the group membership will be reported back to the respective study nurses.
 
Comparison groups:
 
 
- Intervention group: Receives the navigation intervention described below for 1 year from initial interview with Navigator. After randomization, participant is informed about group allocation and receives contact information of the navigator.
 
- Control group: Does not receive support from the navigator. After randomization, the participant will be informed about the group allocation and will receive the brochure with support services for people affected by stroke or lung cancer and their caregivers (see pdf version here: https://navicare.berlin/de/ressourcen-fuer-patienten/).
 
 
Patients in both groups can utilize all standard care services.
 
Patients who decline randomization in the RCT will have the opportunity to participate in a parallel cohort survey.
 
Patients who meet the inclusion criteria but do not wish to participate in any of the study arms will be asked if they would be willing to provide their reasons. They can then fill out a "refuser questionnaire" or communicate their reasons to the study nurse, who will then fill out the questionnaire. Refuser questionnaires can
 |

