|  | 
For the navigation, the navigator will contact the recruited study participants of the intervention arm (up to 4 weeks after inclusion) or will be actively contacted by the participants in case of prior need. The navigator conducts an initial and personal interview with the study participants to identify the individual situation of the study participant and possible pre-existing support needs of the participants, as well as to establish the preferences of the study participants for the further form of interaction and communication. The location of the meeting is determined according to the needs of the study participant(s). This initial meeting will be face-to-face by default (Amendment from August 2021: possibility of video consultation due to pandemic situation) and planned to be of sufficient duration to identify the needs of the study participants and to agree on an individual plan of communication with the study participants as well as the initial frequency of contact. Independently of this, the navigators offer regular telephone consultation hours during which study participants can contact them. Navigation is planned for a duration of 1 year per study participant and the minimum frequency of contact between navigator and study participant is once every 3 months.
 
Tasks of navigation:
 
 
(a) Provide information to support daily living and further support options, such as counseling services, psychosocial and other support options.
 
(b) Help with application formalities, such as applying for a disability certificate or degree of care and rehabilitation measures.
 
(c) If necessary, establishing contact with (specialist) doctors, therapists and other support and care facilities.
 
 
The navigator will document the navigation process in detail with the study participants to obtain data for selected outcomes to
 |

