|  | 
investigate the feasibility of the navigation model.
 
The navigators have weekly team meetings for mutual support and information exchange. These meetings are accompanied by participant observation by a researcher. In addition, expert interviews with the navigators will be conducted as well as guideline-based interviews with study participants to capture how the navigators support study participants and how this is experienced by study participants and navigators.
 
This serves the purpose of process evaluation as well as the identification of possible needs for change in the navigation model.
 
Other data collection methods
 
a. Data collection RCT
 
Questionnaire Assessments:
 
To examine the effectiveness of the intervention, both groups will receive a baseline assessment on the day of study enrollment (if this is not feasible in individual cases, it may be conducted in the period up to 4 weeks after study inclusion). Follow-up interviews will take place 4 months, 7 months and 13 months after inclusion. (Amendment from August 2021 and January 2022: Vital status of patients is accessed from the registration office prior to follow-up and after study completion to identify lost-to-follow-up participants)
 
Questionnaires can be answered in writing by the study participant or with the help of caregivers or study staff if needed.
 
Secondary data analysis
 
The AOK Nordost provides pseudonymized routine data for all participants of the RCT who are insured with the AOK Nordost. These data contain information on individual treatment and care data, frequency of utilization of health care services, and data on associated costs. The
 |

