|  | 
ANCOVA, adjusted for baseline measurement of a selected patient-reported outcome (e.g., health-related quality of life (Authors' comment: defined to outcome 'satisfaction with care' in study registration prior to recruitment start)) and adjusted for the stratification variables of randomization (hierarchical testing). All primary questions are analyzed confirmatory manner in the "full analysis set." In case of missing values and assuming missing at random, multiple imputation models are used to estimate the missing values.
 
In addition to the analyses of primary outcomes described at the outset, additional feasibility criteria will be evaluated descriptively/exploratively as secondary outcomes and patient-reported outcomes (see Table 1-3) will be compared between intervention arms in univariate analyses and multiple regression models. Exploratory subgroup analyses will be conducted to examine differences in feasibility and effectiveness in relation to predefined comparators.
 
b. Cohort Study
We expect the cohort study to have a participation rate of 30% of approached patients who decline to participate in the RCT. This results in 225 stroke patients in the cohort study.
 
Collected data of patient-reported outcomes will be analyzed exploratively/descriptively and compared longitudinally.
 
c. Process evaluation
Process evaluation, including qualitative interviews with study participants, will not require biometric design; rather, sampling will be used to map experiences with the intervention until study results are considered saturated. Experience from other qualitative studies suggests that the
 |

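### A baseline questionnaire taken up to 4 weeks after inclusion can follow disclosure of the arm and navigator contact, so using it as the ANCOVA covariate can bias the efficacy estimate, probably toward no effect

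*Protocol*

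**What the plan says.** Item 8 (planned measures), under data collection for the RCT, states that "both groups will receive a baseline assessment on the day of study enrollment". It then allows an exception: "if this is not feasible in individual cases, it may be conducted in the period up to 4 weeks after study inclusion".

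The order of events is set elsewhere in item 8. Under recruitment: "Participants will be randomized to the intervention arm or the control arm after giving informed consent". Under randomisation: "After inclusion of the patient by the study nurse, randomization will be performed by the Institute of Biometry and Clinical Epidemiology". Neither sentence makes a completed questionnaire a condition of randomisation. For the intervention arm, "After randomization, participant is informed about group allocation and receives contact information of the navigator". For the control arm, "After randomization, the participant will be informed about the group allocation and will receive the brochure with support services". Under intervention, the first navigator contact has a window of the same length, "the navigator will contact the recruited study participants of the intervention arm (up to 4 weeks after inclusion", and a participant who needs help sooner may call first.

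Item 13 (biometric planning, stroke RCT) makes efficacy a hierarchical primary question at two-sided 0.05, tested only after feasibility is shown, by "ANCOVA, adjusted for baseline measurement of a selected patient-reported outcome" and for the stratification variables. An authors' comment fixes the outcome as satisfaction with care. The lung cancer trial is handled by analogy. Missing values are to be multiply imputed under missing at random. Item 9 says that blinding is not possible.

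**The concern.** A baseline covariate is safe in a randomised comparison because it is fixed before the arm can influence it. A late questionnaire here has no such protection. The respondent may already know the arm and, in the intervention arm, may already have met the navigator. The measure is self-reported satisfaction with care, which such knowledge could plausibly move. Item 9 itself foresees disappointment among controls and some short-term relief from navigation. Both would push late scores apart in the same direction.

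Adjusting for a score that already carries part of the arm difference subtracts that part from the estimated effect. A larger sample does not remove the error. The planned multiple imputation does not help either, because a late score is present rather than missing. A same-day questionnaire is not fully secured: nothing says it is answered before allocation is disclosed on that day.

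**Working it through.** **What the plan provides.** The protocol's only sample-size figures are the feasibility thresholds. They reproduce with the Wald interval p ± 1.96 √(p(1−p)/n): for stroke, 166/219 gives 75.8% (70.1% to 81.5%) and 65/196 gives 33.2% (26.6% to 39.8%). The baseline questionnaire is not an input to them. For the efficacy ANCOVA item 13 gives no effect size, SD, correlation or expected share of late baselines, so everything below rests on stated assumptions.

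**Formula.** Work in SD units. Let the true effect be θ, the ANCOVA slope on baseline ρ, the share of late baselines q, and the arm difference already present in late scores g. The adjusted estimate is the difference in outcome means minus the slope times the difference in baseline means. The baseline means differ by q × g, so

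expected estimate = θ − ρ × q × g, and bias = −ρ × q × g.

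The bias is zero if g = 0. If g > 0, the estimate shrinks toward zero.

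**Assumed inputs.** θ = 0.30; ρ from 0.3 to 0.7; g from 0.1 to 0.3. For q, 5% and 10% are taken as readings of the protocol's individual-cases wording, and 25% as a stress value.

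| Late share q | Smallest loss (ρ 0.3, g 0.1) | Middle (ρ 0.5, g 0.2) | Largest (ρ 0.7, g 0.3) |
|---|---|---|---|
| 5% | 0.3×0.05×0.1 = 0.0015 (0.5% of θ) | 0.5×0.05×0.2 = 0.005 (1.7%) | 0.7×0.05×0.3 = 0.0105 (3.5%) |
| 10% | 0.003 (1.0%) | 0.010 (3.3%) | 0.021 (7.0%) |
| 25% | 0.0075 (2.5%) | 0.025 (8.3%) | 0.0525 (17.5%) |

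**Simulation check.** One million simulated participants per scenario with ρ = 0.5 and g = 0.2 gave estimates of 0.2956, 0.2912 and 0.2751 at q = 5%, 10% and 25%. The formula gives 0.295, 0.290 and 0.275.

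**Against the noise.** Item 13 assumes 196 stroke patients alive at one year in the intervention arm; take the same number in the control arm. With ρ = 0.5 the residual SD is √(1 − 0.25) = 0.866, and the standard error is 0.866 × √(2/196) = 0.0875. The middle case at 10% is therefore 0.010/0.0875 = 0.11 standard errors.

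**Power (ρ = 0.5, g = 0.2, two-sided 0.05).**

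| | No bias (0.30) | 10% late (0.290) | 25% late (0.275) |
|---|---|---|---|
| Stroke, 196 per arm | 0.929 | 0.912 | 0.882 |
| Lung cancer, 43 per arm | 0.362 | 0.342 | 0.313 |

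**The case against.** The strongest reply is that same-day baseline is the rule and the exception covers individual cases only. At such shares the loss is a few percent of the effect. The likely direction is conservative: it could hide a benefit, not manufacture one. Feasibility is the leading primary aim, efficacy is tested only after it, and the feasibility criteria do not use the questionnaire. A late baseline may also be answered before the navigator has made any contact. All of this stands, and it limits the weight of the point. It does not remove it, because the protocol sets no cap on late baselines and never places the questionnaire before disclosure. The order of data collection also cannot be repaired by an analysis plan.

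A reader might infer something stronger: that 30% to 50% of baselines will be late and differ by 0.3 to 0.5 SD, so that with a slope of 0.5 the bias is 0.5×0.30×0.3 = 0.045 to 0.5×0.50×0.5 = 0.125 SD, or about 0.5 to 1.4 standard errors. The document does not support this. Such a share is not individual cases, and no source is given for a difference of that size. The January 2022 amendment in item 15 (postal contact and self-initiated enrolment, stroke only) says nothing about questionnaire timing. Item 23 allows written or telephone completion, so remote enrolment does not rule out a same-day answer.

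On cost, it can fairly be said that delaying allocation disturbs a follow-up clock that runs from inclusion. That is correct, and the fix has to deal with it.

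**Conclusion.** The point holds as a gap in sequencing. The protocol permits an unblinded, post-randomisation score to serve as the baseline covariate in the efficacy ANCOVA, directly for stroke and by analogy for lung cancer. This can bias the estimate; it does so only if late scores differ by arm. That is plausible for this outcome but nowhere quantified.

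Under the assumptions shown, the loss is about 0.5% to 7% of a 0.30 SD effect when 5% to 10% of baselines are late, and 2.5% to 17.5% at 25%. It becomes material only from about a quarter of participants. The expected direction is toward no effect, so the documents do not support reading it as a route to a false claim of benefit. Nor do they support treating it as a threat to the feasibility result. It is worth correcting because the correction is cheap and standard.

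**What to change.** **Conduct.** Require the baseline questionnaire to be completed before randomisation is requested, or at the least before allocation is disclosed and before any navigator contact. Apply this to same-day baselines too.

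**Clock.** Follow-ups now run at 4, 7 and 13 months from inclusion, while the intervention year runs from the first navigator interview. If allocation waits 4 weeks and the interview comes up to 4 weeks after that, the year ends about 12 months plus 8 weeks after inclusion, past the 13-month assessment. In delayed cases, in both arms, count the assessment times from randomisation. State which date the navigator's contact window and the 4-week survival denominator of the first feasibility criterion refer to.

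**Participants already enrolled.** Record each baseline date relative to disclosure. In the primary ANCOVA, treat patient-reported baseline scores dated after disclosure as missing. Fill them by a method that does not use arm (stratum mean or missing indicator), stated as an exception to the planned multiple imputation. Report the as-collected analysis as a sensitivity analysis, with the number of late baselines by arm.

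**Cost.** A short delay of allocation for the few who cannot answer on the day, slightly less precision from the filled baselines, and edits to the randomisation, follow-up and analysis text.

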|                                                                                                                                                                                                                                                             | 
2. lung cancer
 
A total of 195 lung cancer patients and, if applicable, caregivers (male/female/diverse, age <math>\geq 18</math> years) will be included in the overall study.
 
These will be divided among the study parts as follows:
 
a. RCT
120 lung cancer patients (and caregivers, if applicable).
 
b. Cohort study
75 lung cancer patients
 
c. Qualitative study
Study participants from RCT and cohort study
(in addition, 3 study nurses/navigators (male/female/diverse) aged 18 years and older)
 
d. Secondary data analysis
Approx. 43 lung cancer patients from RCT (depending on the actual AOK-insured proportion in the RCT)
                                                                                                                            |
| 
13. Biometric planning with indication of the statistical methodology, including justification of the number of cases. Indication of the statistician (if advice is given by the Institute of Biometry of the Charité, a signature must be included)
 | 
Biometric Planning:
 
Biometric calculations were calculated based on the two defined primary feasibility outcomes for determining feasibility. These are as follows:
 
"The intervention is feasible if:
 
(1) At least 70% of patients* in the intervention arm participated in at least one initial face-to-face navigator session.
 
AND
 
(2) The dropout rate of the intervention arm of the RCT is less than 40% (here, dropouts are defined as study participants who drop out of the intervention for reasons other than those that physically prevent the patient*/caregivers from participating. E.g., move out of catchment area, deterioration in general health, long-term hospitalization, move to nursing home or hospice, death).
 
Explanations in the individual study sections:
 |

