|  | 
1. Stroke
 
a. RCT
 
For the duration of the recruitment period, we expect a population of about 1850 stroke patients at the three planned recruitment sites (1100 patients at Charité Universitätsmedizin Berlin stroke units at the sites Mitte and Virchow Klinikum, 750 patients at Asklepios Fachklinikum Brandenburg (Amendment from August 2021: Changed to Klinik Hennigsdorf due to change of cooperating physician)) based on data from previous years. We assume that 70% of these patients can be approached by the study personnel for participation in the study. Of the patients approached, we expect a recruitment rate (depending on recruitment site) of 30-50%. Based on these assumptions, we expect 460 stroke patients (and their caregivers) to participate. Based on the feasibility criteria defined above, the statistical planning is as follows: If 460 stroke patients are included in the study, and 230 (50%) of the patients* are randomized to the intervention arm, we assume that at least 95% (n=219) will still have survived to receive patient navigation at 4 weeks. If 166 (75.8%) or more of these 219 patients* receive the initial navigation session, the first feasibility criterion is met, as the 95% confidence interval of this proportion will not be less than 70% (95%CI: 70.1%-81.5%). We additionally assume that of these 230 patients (intervention arm), 85% (n=196) survived after one year. If of these 196 patients, 65 (33.2%) or less are "lost-to-follow-up", the second feasibility criterion will be met, as the 95% confidence interval of this proportion will be less than 40% (95% CI: 26.6%-39.8%).
 
The feasibility of the study is considered successful if both criteria are achieved.
 
In case of successfully demonstrated feasibility, we additionally test the efficacy of the intervention in the study at the two-sided significance level <math>\alpha=0.05</math> using
 |

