|  | 
have survived to receive patient navigation at 4 weeks. If 46 (80%) or more of these 57 patients* receive the initial navigation session, the first feasibility criterion is met, as the 95% confidence interval of this proportion will not be less than 70% (95%CI: 70.5%-90.9%). We additionally assume that of these 57 patients (intervention arm), 75% (n=43) survived after one year. If of these 43 patients, 11 (25.6%) or less are lost-to-follow-up, the second feasibility criterion will be met, as the 95% confidence interval of this proportion will be less than 40% (95% CI: 12.5%-38.6%). The feasibility of the study is considered successful if both criteria are achieved.
 
Analogous to the stroke study, if feasibility is successfully demonstrated, the efficacy of the intervention with respect to a selected patient-reported outcome (e.g., health-related quality of life (Authors' comment: defined to outcome 'satisfaction with care' in study registration prior to recruitment start)) is additionally tested as a primary question at the two-sided significance level of <math>\alpha = 0.05</math> (hierarchical testing). If feasibility cannot be demonstrated, all other outcomes will be analyzed secondarily in an exploratory manner.
 
In addition to the analyses of primary outcomes described at the outset, additional feasibility criteria will be evaluated descriptively/exploratively as secondary outcomes and patient-reported outcomes will be compared between intervention arms in univariate analyses and multiple regression models. Exploratory subgroup analyses will be conducted to examine differences in feasibility and effectiveness related to predefined comparators.
 
b. Cohort Study
We expect the cohort study to have a participation rate of 30% of approached
 |

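### The four feasibility cut-offs rest on Wald intervals. Under Wilson or exact limits the participation counts miss 70% and the dropout counts sit on the 40% margin; only lung-cancer participation is materially off.

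*Protocol*

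**What the plan says.** Item 13 of the protocol (Biometric planning) opens with two feasibility criteria. The first is "At least 70% of patients* in the intervention arm participated in at least one initial face-to-face navigator session". The second is a dropout rate below 40% in the intervention arm, not counting dropout for reasons that physically prevent participation. The sections on each RCT then turn these into interval rules with fixed counts.

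- Stroke, participation: "If 166 (75.8%) or more of these 219 patients* receive the initial navigation session, the first feasibility criterion is met", since the 95% interval "will not be less than 70% (95%CI: 70.1%-81.5" per cent).
- Stroke, dropout: 65 or fewer of 196 (33.2%), in which case "the second feasibility criterion will be met, as the 95% confidence interval of this proportion will be less than 40% (95% CI: 26.6%-39.8" per cent).
- Lung cancer, participation: "If 46 (80%) or more of these 57 patients* receive the initial navigation session, the first feasibility criterion is met", with a printed interval of 70.5% to 90.9%.
- Lung cancer, dropout: "If of these 43 patients, 11 (25.6%) or less are lost-to-follow-up, the second feasibility criterion will be met", with a printed interval of 12.5% to 38.6%.

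The interval method is not named. Both criteria must be met for feasibility. Primary questions are to be analysed in a confirmatory manner. Efficacy is tested at two-sided 0.05 only after feasibility has been shown; otherwise all other outcomes are exploratory.

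**The concern.** Each count is said to meet its criterion because a 95% interval excludes 70% or 40%. Whether that is true depends on the interval formula. The Wald interval is symmetric around the observed proportion and takes its variance from that proportion. For proportions away from one half it therefore ends too close to the observed value on the side facing 50%. That is the deciding side in all four rules, and the effect is largest in the lung-cancer trial with bases of 57 and 43.

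At stake is the primary claim of each trial, and with it the gate to a confirmatory efficacy test. In the lung-cancer trial a result of exactly 46/57 counts as met under the printed rule and as not met under Wilson or exact limits. With no method named, the protocol leaves that choice open.

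**Working it through.** **Inputs.** Counts, denominators, margins (70%, 40%) and printed intervals come from item 13, RCT sections for stroke and lung cancer. z = 1.96.

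**1. Reproduce the printed intervals.** Wald: p ± z·√(p(1−p)/n). For 46/57: p = 0.8070, standard error √(0.8070 × 0.1930 / 57) = 0.0523, half-width 0.1025, so 70.5% to 90.9% as printed. The other three also match: 166/219 gives 70.13 to 81.47, 65/196 gives 26.57 to 39.75, and 11/43 gives 12.54 to 38.62. Wilson (with or without continuity correction), Clopper-Pearson, Agresti-Coull and Jeffreys do not reproduce the printed limits. Each cut-off is also the first count that passes under Wald. One patient worse fails: 45/57 has lower limit 68.4%, 165/219 has 69.6%, 66/196 has upper limit 40.3%, and 12/43 has 41.3%.

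**2. Deciding limit under other methods.** Wilson: [p + z²/2n ± z·√(p(1−p)/n + z²/4n²)] / (1 + z²/n). For 46/57 this is 0.7876 ± 0.1010, so 68.66% to 88.87%. Clopper-Pearson: the lower limit solves P(X ≥ x) = 0.025, the upper limit P(X ≤ x) = 0.025.

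| Rule | Margin | Wald | Wilson | Clopper-Pearson | Jeffreys |
|---|---|---|---|---|---|
| Stroke participation 166/219, lower | 70% | 70.13 | 69.71 | 69.57 | 69.81 |
| Stroke dropout 65/196, upper | 40% | 39.75 | 40.02 | 40.23 | 39.96 |
| Lung participation 46/57, lower | 70% | 70.46 | 68.66 | 68.09 | 69.09 |
| Lung dropout 11/43, upper | 40% | 38.62 | 40.24 | 41.17 | 39.91 |

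Agresti-Coull also fails all four (69.70, 40.03, 68.49, 40.38). The participation counts fail under every alternative tried; the dropout counts pass narrowly under Jeffreys.

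**3. Exact one-sided error at the margin.** These binomial tails do not depend on the choice of interval. A two-sided 95% interval implies 2.5% on the deciding side.

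| Rule | Printed count | Error | One patient stricter | Error |
|---|---|---|---|---|
| Stroke participation, p = 0.70 | ≥166/219 | 3.41% | ≥167/219 | 2.40% |
| Stroke dropout, p = 0.40 | ≤65/196 | 2.90% | ≤64/196 | 2.04% |
| Lung participation, p = 0.70 | ≥46/57 | 4.86% | ≥47/57 | 2.41% |
| Lung dropout, p = 0.40 | ≤11/43 | 3.54% | ≤10/43 | 1.62% |

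Lung participation stands out: 4.86 / 2.5 = 1.94. The stricter counts are the first to pass under both Wilson and Clopper-Pearson.

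**4. Dependence on the denominator.** For the first Wald-passing count with n from 50 to 60 at 70%, the exact error runs from 2.9% (n = 56) to 5.7% (n = 52). It is above 2.5% throughout, but the size changes with n.

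**5. Joint claim.** Both criteria must hold, so the joint error cannot exceed 4.86% when true participation is 70%. As an illustration, assume independence and a true lung dropout of 25%: P(X ≤ 11 of 43) = 0.615 and 0.0486 × 0.615 = 3.0%. At 30% dropout, 0.0486 × 0.327 = 1.6%.

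**The case against.** Several counter-arguments carry weight.

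- The counts are conditional planning figures. The denominators 219, 196, 57 and 43 come from assumed enrolment and survival, so the printed cut-offs apply only if those numbers occur. A statistical analysis plan, not shown here, could name the interval. This stands, and it is why the fix must bind the method and not only the counts. The protocol still prints counts at which a criterion is declared met.
- The criteria as first defined are plain proportions, and all four counts satisfy them (75.8%, 33.2%, 80.7%, 25.6%). That is true, but the same item then justifies success by interval exclusion, and it is this justification that fails.
- The 2.5% is inferred. No error level is stated for feasibility, and against a one-sided 5% level all four rules would comply (4.86% at most). The protocol prints two-sided 95% intervals and does not mention a one-sided 5% level.
- The dropout misses are small: stroke exceeds 40% by 0.02 points under Wilson, and mid-P tails are 2.5% (65/196) and 2.6% (11/43).

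A reader might infer that all four rules are seriously wrong, that feasibility would be falsely declared 4.9% of the time, or that the efficacy error is inflated. The documents support none of these. Three of the four excesses are about one percentage point or less, 4.9% is a ceiling for one disease, and the efficacy test keeps its own two-sided 0.05 level.

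**Conclusion.** The point holds in limited form and is a should-fix. The printed intervals are Wald, and none of the four cut-offs excludes its margin under Wilson or Clopper-Pearson limits. The two participation counts fail under every alternative tried; the two dropout counts are borderline and depend on the method. The only material excess is lung participation: 4.9% exact error at 70% against an implied 2.5%.

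This rests on three things: reading the two-sided 95% interval as 2.5% on the deciding side, the planned denominator of 57, and treating 4.9% as an upper bound because both criteria must be met. It does not call for a change in sample size or conduct.

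**What to change.** In item 13, state that the feasibility decision uses two-sided 95% Wilson (or Clopper-Pearson) intervals, applied to the denominators actually observed. Restate the planning counts, which are the same under both methods: stroke at least 167/219 and at most 64/196; lung cancer at least 47/57 and at most 10/43. Replace the printed intervals to match. If a one-sided 5% level was intended, say so and print intervals at that level instead.

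The cost is one clause and four restated counts with their intervals. The downside is that each criterion becomes one patient stricter. At a true lung participation of 80%, the chance of meeting the first criterion falls from P(X ≥ 46 of 57) = 53% to P(X ≥ 47 of 57) = 39%.
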